### Subjects

#### Inclusion criteria

Those who are willing to participate in the trial and meet the following conditions will be included: ages 8 to 9 years old; SE (after cycloplegia), − 0.5 D to + 0.5 D; uncorrected visual acuity ≥ 0.8; corneal curvature, 40 D–46 D; with good compliance; and the subject and his/her guardians signed the informed consent form.

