**Method/design:**

A total of 480 subjects at 8–9 years old will be randomized in a 1:1 ratio to an intervention group versus a control group. The intervention group will receive auricular acupressure for 12 months, while the control group will be taken as a blank control. The primary and secondary outcomes will be measured at baseline, and again at 3, 6, 9, and 12 months after recruitment. The myopia incidence (spherical equivalent ≤ − 0.50 D) and the mean change of spherical equivalent will be taken as the primary variables; the secondary outcome measures include axial length, uncorrected visual acuity, and choroidal and retinal thickness.

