#### Exclusion criteria

Those who meet any of the following conditions will be excluded: combined with other eye diseases (cataract, congenital retinal disease, strabismus, amblyopia, etc.) or systemic diseases; with active eye diseases or had a history of eye surgery; those who have used atropine, orthokeratology lens, or other myopia prevention and control methods; skin lesion at the to-be-treated auricular acupoints or sensitive to the ear adhesive; subjects who cannot cooperate to complete the treatment; and the guardian has unreasonable expectation.

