#### Primary outcome measures

The primary outcome measures include MI and SE.

The measurement of SE will be carried out with Nidek ARK-1 refractometer produced by Nidek, Japan. Before measurement, the subjects were given one drop of 0.5% proparacaine hydrochloride eye drops (Alcaine), one drop of 1% cyclopentolate hydrochloride eye drops (CYCLOGYL) 1 min later, and one drop of 1% cyclopentolate hydrochloride eye drops (CYCLOGYL) 5 min later, to induce cycloplegia, getting ready for automatic optometry 30 min later. The measurement will be performed three times successively. Make sure that the maximum-minimum difference in the spherical and cylindrical diopters should be no more than 0.25 D, respectively, and the average value of the three measurement results will be recorded. The SE is defined as spherical diopter plus 1/2 cylindrical diopter. According to existing reports and clinical routines [35], we define myopia as SE ≤ − 0.50 D.

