### Statistical analysis

SPSS version 25.0 will be used for data processing in this trial. Only ocular parameters of the right eye will be included for statistical analysis. Analyses will be performed based on a modified intention-to-treat principle and involve only subjects who have both a baseline outcome measurement and at least one post-randomization observation. Last-observation-carried-forward approach will be used to replace missing data.

The measurement data will be expressed as means ± standard deviation or median (interquartile interval), and the counting data will be described by the number of cases (percentage). Fisher’s exact test or Pearson’s chi-square test will be used for trial group comparisons of 1-year cumulative MI. Generalized estimating equations (GEE), with one within-subject factor (time), one between-subject factor (intervention), and their interactions, will be used to compare changes in spherical equivalent, axial length, uncorrected visual acuity, and choroidal and retinal thickness. The covariates in the GEE models include the corresponding baseline measures, age, gender, number of myopic parents, outdoor light exposure time, and near-work time. All the tests of effects will be conducted at a two-sided alpha level of 0.05.

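### The SE entry range and the myopia definition overlap at −0.50 D, and the MI analysis is not restricted to children who are non-myopic at baseline

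*Protocol article*

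**What the plan says.** Under Inclusion criteria, the protocol article sets the refractive entry range as "SE (after cycloplegia), − 0.5 D to + 0.5 D". The only other vision-related entry limits are a corneal curvature range and "uncorrected visual acuity ≥ 0.8".

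Under Primary outcome measures it states "we define myopia as SE ≤ − 0.50 D", with the end point included. The Abstract uses the same threshold for MI.

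The Exclusion criteria cover "combined with other eye diseases (cataract, congenital retinal disease, strabismus, amblyopia, etc.) or systemic diseases" and "those who have used atropine, orthokeratology lens, or other myopia prevention and control methods". Myopia at baseline is not named.

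Under Statistical analysis, only the right eye is analysed. The analyses "involve only subjects who have both a baseline outcome measurement and at least one post-randomization observation", and missing values are filled by carrying the last observation forward. For MI, "Fisher’s exact test or Pearson’s chi-square test will be used for trial group comparisons of 1-year cumulative MI". Baseline measures enter as covariates in the GEE models for the continuous outcomes, but not in the MI comparison.

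**The concern.** An incidence counts new cases among people who do not yet have the condition. Here the entry range and the case definition share a value: a child at exactly −0.50 D satisfies both on the same day. Such a child cannot develop myopia during the trial, because the definition is already met.

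If these children are counted as cases, they add to the numerator in both arms without carrying information about prevention. That pulls the MI relative risk towards 1 and costs power in a primary comparison planned at only 80%. The reported figure would also no longer be an incidence in the sense used to size the trial.

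**Working it through.** **1. Does any stated rule remove a child at exactly −0.50 D?**

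| Rule | Effect on a child at −0.50 D |
|---|---|
| SE entry range | Admitted. The age and corneal curvature ranges in the same sentence read as ordinary closed ranges, and the SE limit is not marked as strict |
| Visual acuity limit | Not a refractive limit, so it does not settle the matter |
| Exclusion criteria | Remove other eye disease and earlier users of myopia control, not baseline myopia |
| Elimination criteria | Concern children included by mistake; this child meets the criteria |
| Analysis set | Requires a baseline and one later measurement, not non-myopic status |
| MI test | Unadjusted, with no at-risk denominator stated |

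No rule does.

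**2. The plan's own sample size.** Inputs from Sample size: MI 8.41% (intervention) and 17.65% (control), α = 0.05, power 0.80, ratio 1:1. Statistical analysis says tests are two-sided, so z = 1.96 is used with 0.8416 for power.

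n = (1.96 + 0.8416)² × [0.0841 × 0.9159 + 0.1765 × 0.8235] / (0.0924)² = 7.849 × 0.22237 / 0.008538 = 204.4 per arm.

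The stated 204 is reproduced, and 408 / 0.85 = 480. The planned relative risk is 8.41 / 17.65 = 0.48.

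**3. Effect of children at the bound.** The document gives no share, so f is an assumption. Suppose a fraction f in each arm is at the bound and all are counted as cases, while the remainder follow the planned rates:

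p′ = f + (1 − f) × p

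Power = Φ( |p′₁ − p′₂| / √{[p′₁(1 − p′₁) + p′₂(1 − p′₂)] / n} − 1.96 )

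Worked example, f = 2%:
- p′₁ = 0.02 + 0.98 × 0.0841 = 0.1024
- p′₂ = 0.02 + 0.98 × 0.1765 = 0.1930
- difference 0.0906 and variance sum 0.2477
- n = 204: standard error 0.0348, ratio 2.60, power Φ(0.64) = 0.739
- n = 240: standard error 0.0321, ratio 2.82, power Φ(0.86) = 0.805

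| f | Children of 480 | MI, intervention / control | Relative risk | Power, 204 per arm | Power, 240 per arm | Share of control-arm cases present at baseline (f / p′₂) |
|---|---|---|---|---|---|---|
| 0 | 0 | 8.4% / 17.7% | 0.48 | 80% | 86% | 0% |
| 1% | about 5 | 9.3% / 18.5% | 0.50 | 77% | 83% | 5% |
| 2% | about 10 | 10.2% / 19.3% | 0.53 | 74% | 80.5% | 10% |
| 4% | about 19 | 12.1% / 20.9% | 0.58 | 68% | 75% | 19% |

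Two sample sizes are shown because 204 is the number left after 15% dropout. The analysis set keeps anyone with one follow-up measurement and carries values forward, so up to 480 / 2 = 240 per arm could be analysed. That is an upper limit.

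**4. Restricting MI to children above −0.50 D at baseline.** The planned rates then apply to n × (1 − f). With 204 per arm, power is 79.5%, 79.1% and 78.3% for f = 1%, 2% and 4%. Most of the loss is recovered.

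**The case against.** **Incidence already means new cases.** The document never says that baseline cases are counted, and an at-risk denominator could be set in an analysis plan that is not shown. This has force, and it is why the conclusion is that such children *can* be counted, not that they will be. It does not remove the point: the overlap between the two thresholds is on the page, and the analysis set that is described carries no such restriction.

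**The overlap is one value, not a range.** SE is the mean of three readings, so exact ties may be few. This stands and limits the size.

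**The effect is on one outcome and in one direction.** Baseline data are complete before allocation is disclosed, and SE change is analysed with adjustment for baseline. For a trial that also aims at myopia control, a borderline child is still informative on SE. This stands too.

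A reader might infer more than the text supports:

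- *That children a little below −0.50 D also pass, because the entry limit has one decimal and the definition two.* Nothing says SE is rounded to one decimal before eligibility is judged.
- *That every such child is a case at follow-up whatever the treatment.* A child at the threshold can measure slightly above it later, and the article does not say whether cumulative MI refers to any visit or to month 12. The table makes this assumption and so shows the largest effect for each f.
- *That both arms gain the same number of such cases, or that one arm is favoured.* Randomisation balances them in expectation, not in exact number, and the expected result is dilution.

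**Conclusion.** The point holds as an inconsistency between two stated rules in a primary outcome. A child at exactly −0.50 D can be enrolled already myopic and be counted as a case in the 1-year cumulative MI. The consequence is a weaker MI contrast and a figure that is not strictly an incidence. The documents do not support a claim of bias between arms, and the SE outcome is not affected in the same way.

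The size is unknown and may be small. It depends on the assumed shares of 1% to 4%, on all such children staying classified as myopic, and on the planned rates describing children truly at risk, which cannot be checked from the article. On those assumptions the loss at 204 per arm is about 3 to 12 percentage points of power. With all 240 per arm analysed, power still reaches 80% at a 2% share. This is a should-fix: the size does not make it critical, but the rules conflict and the remedy is nearly free.

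**What to change.** 1. In Inclusion criteria, state the lower limit as cycloplegic SE strictly greater than −0.50 D, written to two decimals, in the right eye, which is the eye analysed.
2. In Statistical analysis, define the MI denominator as children whose pre-randomisation right-eye SE is greater than −0.50 D.
3. Keep any child already enrolled at the bound in the SE analysis.

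The restriction uses a measurement taken before allocation is disclosed, so it preserves the randomised comparison for MI. The 204 / 408 / 480 target can stay, since its rates are stated as incidences. The cost is a short amendment and a few borderline children fewer in the MI analysis.

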#### Exclusion criteria

Those who meet any of the following conditions will be excluded: combined with other eye diseases (cataract, congenital retinal disease, strabismus, amblyopia, etc.) or systemic diseases; with active eye diseases or had a history of eye surgery; those who have used atropine, orthokeratology lens, or other myopia prevention and control methods; skin lesion at the to-be-treated auricular acupoints or sensitive to the ear adhesive; subjects who cannot cooperate to complete the treatment; and the guardian has unreasonable expectation.

#### Elimination criteria

Those who do not meet the inclusion criteria or match the exclusion criteria but were mistakenly included and have no post-randomization observation.

#### Suspension criteria

Serious adverse events occur and the observation cannot continue; severe complications or special physiological changes occur, and the study cannot continue.

#### Dropout criteria

Despite the reason, the subject or guardian is unwilling or impossible to continue and proposes to withdraw from the study; those who did not propose to withdraw from the study but fail to complete the whole treatment.

#### Recruitment

We will recruit most of the subjects by placing posters in schools, hospitals, and communities, while the rest will be recruited at the outpatient. All the recruitment advertisements will only be published after the trial was approved by the ethics review committee. The respondents will contact the research staff by telephone, WeChat, or in outpatient visit. The researchers will screen the subjects according to the inclusion and exclusion criteria, and collect a part of the baseline data during the screening. The recruitment process will continue until the number of recruits reaches the expected standard. The recruitment process is shown in Figure S1.

#### Sample size

So far, there is no high-quality randomized controlled trial (RCT) studying the sole use of auricular acupoints in reducing the MI. Increasing outdoor time is the main method well recognized in the prevention of myopia. Therefore, the preventive effect of outdoor activities is used to estimate the efficacy of auricular acupoints. The MI in the intervention group 8.41%/year, and that in the control group is 17.65%/year [32]. When we set α = 0.05, test efficiency 1 – β = 0.80, and the ratio between the two groups 1:1, the calculated required sample size is 204 for each group according to the following equation, that is 408 in total. Then, when the dropout is set at 15% or less, a total of 480 participants should be recruited in this study.
$$ n=\frac{{\left({\mathrm{Z}}_{1-\alpha }+{\mathrm{Z}}_{1-\beta}\right)}^2}{{\left({\pi}_r-{\pi}_c\right)}^2}\left[{\pi}_r\left(1-{\pi}_r\right)+{\pi}_c\left(1-{\pi}_c\right)\right] $$$$ {\pi}_r= MI\ \mathrm{in}\ \mathrm{the}\ \mathrm{intervention}\ \mathrm{group} $$$$ {\pi}_c= MI\ \mathrm{in}\ \mathrm{the}\ \mathrm{control}\ \mathrm{group} $$

### Randomization and grouping

SPSS version 25.0 will be used to generate random numbers and random distribution table. According to the random sequence, the paper marked with intervention group or control group will be put into a sealed opaque envelope. The subjects will be randomized into an intervention group or a control group at 1:1. The randomization process will be completed by a third party unrelated to the study. Only after the informed consent of the subjects has been obtained and the subjects have completed the baseline data collection, the allocation personnel can inform the acupuncturists of the allocation assignment.

### Blinding

Due to the unique feature of the intervention, we can only blind the examiners, data processors, and statisticians but not the interveners or subjects. Before each examination, subjects in the intervention group will be asked to take off the auricular adhesives, which will be checked by the personnel in charge of randomization. During the whole study, the subjects and other researchers are not allowed to disclose the grouping to examiners, data processors, and statisticians. Only when serious adverse events occur and the researchers believe that it is necessary to know the intervention to take effective measures, can the blinding rule be broken. The researchers will be trained strictly before the trial begins.

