Operation is as follows: After standard sterilization for the auricular acupoints with 75% alcohol, the auricular adhesives are attached to the acupoints with the pellets precisely targeting the acupoints, eye (LO_5_), liver (CO_12_), kidney (CO_10_), heart (CO_15_), spleen (CO_13_), and shenmen (TF_4_), and pressed tightly. This process will be operated by professional acupuncturists after unified training. The guardian is asked to press the adhesives once every day in the morning (6:30 am–7:30 am), after school (4:00 pm–5:00 pm), and before bed time (9:00 pm–10:00 pm). A good adherence is defined as “completing at least 5 times of acupressure operation during two consecutive days (required to do 3 times a day)”. Each acupoint should be pressed 20 times each session, and the press should be causing distending and aching sensation but within the kid’s tolerance. Every night, the guardian should record the completion status in the diary card, and send the diary card photos to the researcher through WeChat every week. One ear is treated each time (to be alternately at each visit), and the auricular adhesives are changed by the acupuncturist each week. Since the adhesives may fall off due to exercise, bathing and other unexpected conditions, the researcher would send the auricular acupoint atlas and the video on auricular point sticking to the guardian after recruitment, so as to guide the guardian to re-apply the plaster to the original spot after the adhesive falls off. If skin abrasion or swelling occurs at the treated spots during, the guardian needs to contact the acupuncturist immediately to deal with it, which will be recorded in the case report form (CRF).

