#### Control group

The subjects in the control group will not receive any interventions for myopia prevention or control within 12 months, but only go to the hospital to check the relevant optical indicators at the required time points.

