### Safety evaluation

In case of any adverse reaction during the treatment, the subject should contact the researchers immediately. The researchers will diagnose and deal with the adverse reactions, making decision whether it is necessary to stop the test or provide corresponding compensation, and judging if the adverse reaction is caused by auricular acupressure. The adverse reactions included topical ear pain, swollen ear skin, ear skin lesion, palpitation, or nausea. All adverse events should be recorded in the CRF for later analysis.

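### Examiner masking rests on removing the adhesives in one arm only, so marks left on the ear could sometimes show an examiner which children were treated

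*Protocol article*

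**What the plan says.** The Blinding section of the Protocol article limits masking: "we can only blind the examiners, data processors, and statisticians but not the interveners or subjects". To keep examiners masked it sets one physical step: "Before each examination, subjects in the intervention group will be asked to take off the auricular adhesives". The removal is then verified by staff who handle the allocation and are not the examiners. The only other safeguard in routine running is a rule on what people may say: "the subjects and other researchers are not allowed to disclose the grouping to examiners, data processors, and statisticians".

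The Control group section describes no ear procedure. Controls "only go to the hospital to check the relevant optical indicators at the required time points".

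Two other sections foresee visible changes to the ear. The Intervention group section has an instruction that begins "If skin abrasion or swelling occurs at the treated spots during". The Safety evaluation section lists what may happen: "The adverse reactions included topical ear pain, swollen ear skin, ear skin lesion, palpitation, or nausea".

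**The concern.** With no sham and with open allocation for children and acupuncturists, examiner masking is one of two protections at the point of measurement. The other, named in the Discussion, is the use of objective, quantitative indices. The masking step deals with the device. It does not deal with what the device and repeated pressing may leave on the skin, and such marks could appear in one arm only. A ban on disclosure does not hide what can be seen.

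At stake is mainly the outcome that a person scores. If an examiner recognises some treated children, prompting, patience and borderline calls on the acuity chart could differ between the arms, and a reader of the results could not rule this out.

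**Working it through.** No figure in the article bears on this point, and none is needed. The check is a reading of the sections against one another.

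1. **What the step hides.** Blinding has the adhesives taken off before each examination. It gives no interval between removal and measurement, so the article does not tell us whether a mark would have time to fade.

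2. **What may remain.** The Intervention group section prescribes six acupoints on one ear, 20 presses per point per session and three sessions a day. That is 6 × 20 × 3 = 360 presses a day on the ear in use, firm enough to be felt as aching, for 12 months. Ears alternate, and the adhesives are changed weekly. Alternation rests one ear at a time, but the other has been in use up to the removal, and a mark on either ear would be enough. The Intervention group and Safety evaluation sections both name skin changes as possible. Neither says how often they occur.

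3. **Who is near the ears.** Under Secondary outcome measures, the examinee's chin and forehead are placed on instrument brackets for axial length and for OCT, and the eye position is adjusted. Staff taking these measurements work close to the head.

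4. **Which visits are exposed.** Allocation is released only after baseline data are complete (Randomization and grouping), so baseline is not affected. The four visits at 3, 6, 9 and 12 months are.

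5. **Which outcomes are exposed.**

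| Outcome | How it is obtained | Room for examiner influence |
|---|---|---|
| Spherical equivalent and myopia incidence (primary) | Autorefractor under cycloplegia, mean of three readings | Little |
| Axial length | IOL-Master, mean of three readings | Little |
| Retinal and choroidal thickness | OCT, layers detected by built-in software | Little |
| Uncorrected visual acuity | Chart read line by line to a person | Some, within fixed rules on time and misreads |

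The one-arm step and the foreseen skin changes are both in the text. Together they make recognition possible at the four post-baseline visits. The last column places the consequence mainly in visual acuity.

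**The case against.** The strongest reply has four parts.

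- **The article does not say the ears are uncovered.** It is silent, and ear covering is the kind of detail a full protocol might hold. This stands as a limit: visible ears are an inference. What the article does fix is a masking procedure for one arm that ends with removal and a check.
- **Only treated children have anything to remove, and the check is done by people who are not the examiners.** This also stands. A reader might infer that the check itself gives the arm away, but no section places it in the examiner's sight. The remaining gap is the skin, not the check.
- **Marks are conditional and of unknown frequency.** This is correct. It limits the point to recognition that could happen sometimes; it does not remove it.
- **The main outcomes come from instruments.** This is correct and decides the scope. A reader might go further and infer that the primary result is biased, because an examiner could steer the autorefractor readings under the rule that the "maximum-minimum difference in the spherical and cylindrical diopters should be no more than 0.25 D". The article does not support that. It asks for three successive readings and their average, and the criterion concerns the spread of the readings, not their value. Nor does anything in it show that errors would consistently favour one arm.

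For acuity, the time limit and misread allowances narrow the examiner's discretion without removing it.

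**Conclusion.** The point holds as a modest, inexpensive improvement to the design. The article's masking step hides the adhesive and leaves open that an examiner could sometimes recognise a treated child from marks the article itself foresees. The exposure is mainly in uncorrected visual acuity, a secondary outcome. No numerical size is given, because neither the frequency of visible marks nor their effect on scoring is in the document.

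The conclusion rests on two assumptions: that the ears are not covered by a procedure described elsewhere, and that some marks last from removal to examination. It is not a finding that masking fails in practice or that the primary comparison is biased.

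**What to change.** Amend the Blinding section so that, at every post-baseline visit:

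- every child in both arms goes through the same ear check before examination, done by the non-examining staff who already check the intervention arm, and out of the examiner's sight;
- every child then wears an identical opaque covering over both ears for all measurements, of a type that leaves the forehead free for the brackets used for axial length and OCT.

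The cost is a supply of simple covers, a sentence or two in the procedures, and about a minute more per control visit, or roughly 4 × 1 = 4 minutes per control child over the year. No extra staff are needed. If the ears are already covered in practice, stating so would settle that part. The change does not address the child's own knowledge of the allocation, which remains the limitation that the Discussion concedes.
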